### Serious adverse events (SAEs)

A serious adverse event is any untoward medical occurrence or effect that

- results in death;
- is life threatening (at the time of the event);
- requires hospitalisation;
- results in persistent or significant disability or incapacity;
- any other important medical event that did not result in any of the outcomes listed above due to medical or surgical intervention but could have been based upon appropriate judgement by the investigator.

An elective hospital admission will not be considered as a serious adverse event.

The sponsor will report the SAEs through the web portal *ToetsingOnline* to the accredited METC that approved the protocol, within 7 days of first knowledge for SAEs that result in death or are life threatening followed by a period of maximum of 8 days to complete the initial preliminary report. All other SAEs will be reported within a period of maximum 15 days after the sponsor has first knowledge of the serious adverse events.

### Suspected unexpected serious adverse reactions (SUSARs)

### Not applicable.

## Annual safety report

## Not applicable.

## Follow-up of adverse events

All AEs will be followed until they have abated, or until a stable situation has been reached. Depending on the event, follow up may require additional tests or medical procedures as indicated, and/or referral to the general physician or a medical specialist.

SAEs need to be reported till end of study within the Netherlands, as defined in the protocol

## Data Safety Monitoring Board (DSMB)

The Clinical Trial Center Maastricht (CTCM) will be monitoring the study for its safety. It’s an independent committee and it has no conflict of interest with the sponsor of the study . The advice(s) of the DSMB will only be sent to the sponsor of the study. Should the sponsor decide not to fully implement the advice of the DSMB, the sponsor will send the advice to the reviewing METC, including a note to substantiate why (part of) the advice of the DSMB will not be followed.

# STATISTICAL ANALYSIS

The baseline values (gender, age, quality of life, smoking status, diabetes) will be analysed and explained in table 1 of the article. The means and standard deviations of the continuous variables and the numbers and percentages of the categorical variables will be measured. A P-value will be indicated by the use of an unpaired t-test (continuous variables) and a X^2^ test (categorical variables). Variables at baseline that show (statistical significant) differences between intervention group and control group, will be added in the multivariate analysis.

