## Randomisation, blinding and treatment allocation

Patients are randomized with baseline stratification (by gender, age, smoking status and diabetes) into the intervention group or the control group. For concealed allocation of the participants, a computer-generated list of random numbers will be used, which is accessible at both Zuyderland locations. Blinding of patients and researchers is not possible in this case.

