## Primary study parameter(s)

The continuous variables will be presented as quantitative variables. The ANCOVA will be used to adjust for baseline values. A P-value of less than 0.05 was considered statistically significant. Patients were analysed based on per protocol principles.

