## Secondary study parameter(s)

The categorical data will be presented as qualitative variables. Starting with a univariate analysis, the X^2^ test will be used for the binary variables. A risk ratio, including 95% confidence intervals, will be used to indicate the probability of a dislocation of the fracture in comparison to both groups. Thereafter, we will use a multivariate logistic regression analysis, at which the odds ratio will adjust for baseline values. A P-value of less than 0.05 was considered statistically significant. Patients were analyzed based on per protocol principles.

If there is a suspicion of a dislocation of the fracture, based on the assessment of the radiograph and low functional outcome scores, a Computed Tomography (CT) of the ankle will be made to confirm this. Thus, we want the type I error to be controlled.

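### Choosing model covariates by baseline significance tests is unsound, tends to omit the stratification factors, and conflicts with the unconditional adjustment in Sections 10.1 and 10.2

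*Protocol*

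**What the plan says.** Section 10 names five baseline variables: "The baseline values (gender, age, quality of life, smoking status, diabetes) will be analysed and explained in table 1 of the article". Each is compared between the arms: "A P-value will be indicated by the use of an unpaired t-test (continuous variables) and a X^2^ test (categorical variables". The selection rule follows: "Variables at baseline that show (statistical significant) differences between intervention group and control group, will be added in the multivariate analysis". No threshold is given for these tests; 0.05 is the level used for the outcomes.

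Section 8.2 describes the allocation: "Patients are randomized with baseline stratification (by gender, age, smoking status and diabetes) into the intervention group or the control group". The mechanism is given as "a computer-generated list of random numbers will be used, which is accessible at both Zuyderland locations", with no block size, minimisation or age cut-points.

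Section 10.1 says of the primary outcome: "The ANCOVA will be used to adjust for baseline values". Section 10.2 says of dislocation, after an unadjusted risk ratio: "we will use a multivariate logistic regression analysis, at which the odds ratio will adjust for baseline values". Neither section names the baseline values. Section 10.3 plans the same ANCOVA for the other continuous outcomes, and Section 10.4 applies the same methods at an interim analysis. Table 1 in Section 3 schedules OMAS and every other continuous outcome at t1.

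**The concern.** Among patients as randomised, a significant baseline difference is a chance finding. Its p-value says nothing about whether the variable predicts OMAS, and that is what makes a covariate worth having. A rule based on the p-value has three faults.

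- The covariate set is known only after the arms have been compared, and it could differ between the interim and the final analysis.
- Four of the five tested variables are the stratification factors. Stratification is meant to remove imbalance, and the rule admits a variable when it is imbalanced. The better the stratification works, the less likely these factors are to enter through the rule.
- The rule is conditional, while the adjustment in Sections 10.1 and 10.2 is not. Two analysts could fit different primary models and both claim to follow the protocol.

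At stake is precision in a trial planned with 50 patients, and a primary model that is settled before the data are seen.

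**Working it through.** **The plan's own figures.** The protocol gives no figure for the covariate rule. Section 4.4 gives 23 per group for 80% power at 0.05 and a total of 50. (The same sentence also gives 46 per group, which does not fit a total of 50; I use 50.) The means and SD behind the 23 are not stated, so it cannot be reproduced. Solved backwards with a two-sided normal approximation, it implies a standardised difference of √(2/23) × (1.960 + 0.842) = 0.826. I use this as the true effect.

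**How often a variable enters.** With independent tests at 0.05 and no balancing, the chance that at least one of the four factors is significant is 1 − 0.95⁴ = 18.5%. For at least one of all five variables it is 1 − 0.95⁵ = 22.6%. Balancing lowers both.

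**Simulation.** N = 50, 1:1, 4,000 trials per scenario. The following are assumptions, not in the protocol:
- half the patients are women; age has mean 48 and SD 17 and is stratified at 48; 25% smoke; 10% have diabetes;
- the four factors together explain 10% or 30% of OMAS variance, in equal shares;
- quality of life is unrelated to the outcome;
- allocation uses blocks of 4 or 2 within strata, or equal arms drawn without regard to strata.

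Two linear models were compared on the same simulated trials. One was adjusted for the variables significant at baseline, the other always for the four factors. t1 OMAS was in neither.

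| Allocation | Variance explained | At least one of the four enters | Type I error, rule / four factors | Power, rule / four factors |
|---|---|---|---|---|
| Blocks of 4 | 10% | 1.9-2.2% | 0.040 / 0.046 | 0.814 / 0.832 |
| Blocks of 4 | 30% | 2.0% | 0.026 / 0.043 | 0.832 / 0.916 |
| Blocks of 2 | 10% | 0.7-0.9% | 0.037 / 0.048 | 0.814 / 0.837 |
| Blocks of 2 | 30% | 0.5-0.6% | 0.028 / 0.049 | 0.838 / 0.929 |
| No balance within strata | 10% | 20.0-20.2% | 0.045 / 0.047 | 0.812 / 0.829 |
| No balance within strata | 30% | 19.3-20.4% | 0.036 / 0.046 | 0.822 / 0.899 |

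Quality of life, which is not stratified, entered in about 5% of trials throughout. The simulation error is about √(0.026 × 0.974 / 4000) = 0.0025 on a type I error of 0.026, and √(0.83 × 0.17 / 4000) = 0.006 on a power of 0.83.

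**Check on the direction.** If the factors are perfectly balanced but left out, the reported standard error reflects the full variance while the estimate varies with only 1 − R² of it. The type I error is then about 2 × [1 − Φ(1.96/√(1 − R²))], which is 0.039 at R² = 0.10 and 0.019 at R² = 0.30. The simulated 0.040 and 0.026 with blocks of 4 lie between these limits and 0.05, as expected when balance is good but not perfect.

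**Power lost under the rule.** With blocks of 4: 0.832 − 0.814 = 1.8 points at 10%, and 0.916 − 0.832 = 8.4 points at 30%. With blocks of 2: 2.3 and 9.1 points. These differences are net of the degrees of freedom spent on the covariates.

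**The case against.** The strongest reply is that the selection rule does not say that other variables stay out. Sections 10.1 and 10.2 adjust for baseline values without condition, and Section 10 uses that same term for the five listed variables. Read literally, all four stratification factors are already in the ANCOVA. This stands in part. A reader might infer that the stratification factors will almost never be adjusted for; the documents do not support that. What they show is a conflict: if all five variables are always in, the selection rule has no function, and if the rule governs, the later sections do not mean what they say.

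That inference also needs allocation that balances within strata, and Section 8.2 states no blocking. Without such balance, at least one factor enters in about one trial in five. With it, the rule nearly always gives the same model, so the dependence on chance is then small and the 22.6% does not apply.

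The size rests on an assumed share of variance and on models without t1 OMAS. If the planned ANCOVA contains t1 OMAS, what counts is what the factors add beyond it, and the gain is smaller where they share variance. This stands.

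The absence of OMAS from the Section 10 list might be read as excluding it from the model. That list describes a table in the article, and OMAS is measured at t1, so this is an ambiguity and not an exclusion.

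Finally, the analysis is per protocol, so baseline differences in the analysed groups need not be pure chance. That does not rescue the rule: with about 23 per arm a significance test can easily miss an imbalance that matters.

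**Conclusion.** The rule should go. It selects on the wrong criterion, it tends to drop the factors used for stratification, and it cannot be reconciled with Sections 10.1 and 10.2 as written. Because the protocol itself states the rule, an unseen analysis plan does not settle the matter: it would either inherit the rule or contradict it.

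The size is modest to moderate. Under effective stratification about 2 points of power are lost if the four factors explain 10% of OMAS variance, and 8 to 9 points if they explain 30%. Both shares are assumptions, as are the block sizes and prevalences, and the loss is smaller if t1 OMAS is in the model and shares that variance. A reader might infer a raised false-positive rate from data-driven selection. None appeared: the type I error under the rule was below 0.05 in every scenario. The harm is lost precision and a model not fixed in advance.

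**What to change.** Delete the significance-based selection rule in Section 10. State one fixed ANCOVA for OMAS in Section 10.1, with arm, t1 OMAS, gender, age (continuous), smoking status and diabetes, fitted whatever the baseline table shows. In Section 10.3 use the same four factors with each continuous outcome's own t1 value. Once the rule is gone, baseline p-values serve no analytic purpose.

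Do not carry this covariate set over to dislocation. Section 11.4 expects few or no such events, so a logistic model with that many terms may not be estimable. In Section 10.2 keep the unadjusted risk ratio with its confidence interval as the main result, and limit any adjusted model to a small set named in advance.

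The cost is wording, since all the variables are already collected, plus a few degrees of freedom. With 46 patients analysed, the full model leaves 46 − 7 = 39 residual degrees of freedom, against 46 − 3 = 43 with arm and t1 OMAS alone.

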## Primary study parameter(s)

The continuous variables will be presented as quantitative variables. The ANCOVA will be used to adjust for baseline values. A P-value of less than 0.05 was considered statistically significant. Patients were analysed based on per protocol principles.

## Secondary study parameter(s)

The categorical data will be presented as qualitative variables. Starting with a univariate analysis, the X^2^ test will be used for the binary variables. A risk ratio, including 95% confidence intervals, will be used to indicate the probability of a dislocation of the fracture in comparison to both groups. Thereafter, we will use a multivariate logistic regression analysis, at which the odds ratio will adjust for baseline values. A P-value of less than 0.05 was considered statistically significant. Patients were analyzed based on per protocol principles.

If there is a suspicion of a dislocation of the fracture, based on the assessment of the radiograph and low functional outcome scores, a Computed Tomography (CT) of the ankle will be made to confirm this. Thus, we want the type I error to be controlled.

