# INTRODUCTION AND RATIONALE

Ankle fractures are among the most common fractures of the lower extremities. With 9% of all fractures, they account for an important part of the traumatic injuries.^1^ A consideration between an operative vs. conservative treatment has to be made. A distinction must be made between stable and unstable ankle fractures.^2^ The fracture is stable if there is a dislocation of less than 3 millimetres at the ‘medial clear space’ (the jointspace between the medial malleolus and the talus) with a symmetrical ankle fork on the Mortise X-ray.

Classifications are used to describe the mechanism behind the ankle fracture and thus to make a statement about the (in)stability of the ankle joint. A common type of injury is the Weber B fracture or according to the Lauge-Hansen classification the supination-eversion type, that can be stable (SE type 2 without rupture of the deltoid ligament) and also possibly unstable (SE type 4 with rupture of the deltoid ligament). This ligament has a superficial and a deep layer. The superficial layer resists plantar flexion and external rotation of the talus relative to the tibia. The deep layer has anterior and posterior components, the anterior and posterior talo-tibial ligaments (ATTL and PTTL), of which the posterior ligament is the strongest. The PTTL is tight when the foot is plantigrade and loose when the foot is plantar flexed. If however, the foot is plantigrade, as on an anteroposterior weight-bearing radiograph, the intact PTTL will prevent lateral translation of the talus and the ankle fork appears congruent.^3^ Therefore, Gougoulias N. et al. (2017) proposed that a (ligamentous) SE type 4 ankle fracture, one without a medial malleolar fracture, with a ruptured superficial and/or ATTL, but an intact PTTL, can be classified as a ‘SE type 4A’ fracture. This is a stable fracture, as long as the foot is in a plantigrade position. With a complete rupture of the superficial and deep components (both ATTL and PTTL) of the deltoid ligament, the medial clear space will open in all positions of the foot, thus also on weight-bearing radiographs. This type of fracture can be classified as SE type 4B, which is always an unstable fracture.

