**Intervention group**

The dorsal lower limb cast will be removed by the plaster technician. Patients will get a Walker by which they can start with permissive weight bearing. According to protocol, they receive daily thromboprophylaxis (Fragmin 5000IE s.c.). After 6 weeks posttraumatic, the Walker will be removed at the traumatology department. The patients may then extend the weight bearing to functional.

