**Follow-up**

The patients will visit the traumatology department after 6 weeks ***(= t2)*** and 12 weeks ***(= t3)*** posttraumatic. During the visit after 6 weeks, radiographs of the ankle joint are obtained at 3 different views (anteroposterior (AP), lateral and Mortise). Furthermore, they will undergo a comprehensive examination that will include assessment of ankle dorsal flexion/ plantar flexion with use of a goniometer. The circumference of the calf will be measured with a tapeline. This will be performed by the trained research staff or by doctors trained and instructed by them.

Each visit ***(t1, t2 ánd t3)*** the patients receive 2 questionnaires with regard to return to work or sport, daily activities and limiting factors.

[figure not shown]

Figure 1. Flowchart

[figure not shown]

Figure 2. Timeline

| Variable (outcome measure) | Type | t1 | t2 | t3 | Total |
| --- | --- | --- | --- | --- | --- |
| Functional outcome score (OMAS, 0-100) | continuous | ✓ | ✓ | ✓ | 3 |
| Dislocation of the fracture (Yes/No) | binary | ✓ | ✓ | × | 2 |
| Range of motion of the ankle (degrees) | continuous | ✓ | ✓ | ✓ | 3 |
| Circumference of the calf (cm) | continuous | ✓ | ✓ | ✓ | 3 |
| Return to work (%) | continuous | ✓ | ✓ | ✓ | 3 |
| Satisfaction (SF-36, 0-100) | continuous | ✓ | ✓ | ✓ | 3 |
| Other complications | nominal | × | ✓ | ✓ | 2 |

Table 1. Measurements

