# METHODS

## Study parameters/endpoints

### Main study parameter/endpoint

Functional outcome scores of the ankle. This will be indicated with the Olerud/Molander Ankle Function Score (OMAS). This is a continuous variable (0-100 points).

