### Secondary study parameters/endpoints

Dislocation of the fracture within 6 weeks (after placement of the Walker or circular lower limb plaster cast). This is a dichotomous variable (yes/no).

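### Confirmation of fracture dislocation is tied to a low score on the unblinded primary outcome, and the endpoint's 6-week window runs past the last scheduled radiograph

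*Protocol*

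**What the plan says.** **Case confirmation.** Section 10.2 (Secondary study parameter(s)) says that suspicion of a dislocation is "based on the assessment of the radiograph and low functional outcome scores", and that a CT is then made as confirmation. The reason given follows directly: "Thus, we want the type I error to be controlled". No cut-off for a low score and no radiographic criterion for displacement is given.

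**The score in that rule.** Section 8.1.1 makes the functional score the primary endpoint: "This will be indicated with the Olerud/Molander Ankle Function Score (OMAS"), scored 0 to 100. Section 8.2 states that neither patients nor researchers can be blinded. Hypothesis 1 (section 2) expects earlier functional benefit in the intervention group. Null hypothesis 2 is that the Walker is less safe because more dislocations are reported with it.

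**Time window.** Section 8.1.2 defines the endpoint as "Dislocation of the fracture within 6 weeks (after placement of the Walker or circular lower limb plaster cast"). Under Follow-up in section 3, "During the visit after 6 weeks, radiographs of the ankle joint are obtained at 3 different views". That visit is counted from the injury; for the Walker arm, for example, "After 6 weeks posttraumatic, the Walker will be removed at the traumatology department". Table 1 schedules dislocation at t1 and t2 and not at t3.

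**The concern.** Dislocation is the sole endpoint listed as secondary, and Null hypothesis 2 rests on it. If confirming a case requires a poor score on the outcome that the Walker is expected to improve, the same displacement on film is less likely to be confirmed in the Walker arm. The Walker count would then fall for a reason unrelated to safety, in the direction that rejects Null hypothesis 2. Because the OMAS comes from a questionnaire filled in by unblinded patients, expectations about treatment can also enter the safety count.

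The stated rationale does not help. CT confirmation can reduce false-positive diagnoses. Adding a score condition lowers the sensitivity of case finding, possibly by different amounts in the two arms. Neither sets the type I error of the between-arm test, and unequal case finding distorts it.

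The second problem is timing. If the window is counted from placement and the last film is timed from injury, part of the stated window has no scheduled imaging.

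**Working it through.** **1. Which cases are confirmed.** Reading the two conditions in section 10.2 as both required:

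| Radiograph | OMAS | Under section 10.2 |
|---|---|---|
| Suspicious | Low | CT to confirm |
| Suspicious | Good | No CT under this rule; how it is counted is not stated |
| Not suspicious | Any | No suspicion |

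The second row is the gap. A better average OMAS in the Walker arm moves patients from the first row to the second.

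**2. How large the effect could be (illustration).** Suppose second-row cases are not counted. Let s_c and s_t be the probabilities of a low score among patients with a suspicious film in the cast and Walker arms. Then

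apparent RR = true RR × s_t / s_c.

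The protocol gives neither probability, so a shift has to be assumed. Section 4.4 states 23 per group, 80% power and 0.05, without means, SD or sidedness, so its figure cannot be reproduced. It can only be back-solved, assuming a two-sided test:

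- Normal approximation: d = (1.960 + 0.842) × √(2/23) = 0.826.
- t-test: d = 0.845.
- If one-sided (normal approximation): d = 0.73.

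Take normally distributed scores, a true RR of 1, and a difference d between the arms among dislocated patients. Then s_t = Φ(z(s_c) − d). For example, with s_c = 0.50 and d = 0.826, s_t = Φ(−0.826) = 0.204, and 0.204 / 0.50 = 0.41.

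| s_c | Apparent RR, d = 0.826 | Half shift, d = 0.413 | No shift |
|---|---|---|---|
| 0.25 | 0.27 | 0.55 | 1 |
| 0.50 | 0.41 | 0.68 | 1 |
| 0.75 | 0.59 | 0.80 | 1 |
| 0.90 | 0.75 | 0.90 | 1 |

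With d = 0.845 the full-shift values for the first three rows are 0.26, 0.40 and 0.58. The range is therefore about 0.26 to 0.90 under a non-zero shift, and 1 if dislocated patients score equally low in both arms.

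If the endpoint does not depend on OMAS, s_t = s_c = 1 and this distortion disappears.

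**3. Window.** Inputs: t1, when the Walker or cast is placed, is at day 7 to 10 after trauma (section 3); entry is excluded beyond day 14 (section 4.3); t2 is at 6 weeks after trauma, day 42.

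| Placement day | Days from placement to t2 film | End of 42-day window | Days without scheduled film |
|---|---|---|---|
| 7 | 42 − 7 = 35 | day 49 | 7 (7/42 = 17%) |
| 10 | 42 − 10 = 32 | day 52 | 10 (10/42 = 24%) |
| 14 (entry limit) | 42 − 14 = 28 | day 56 | 14 (14/42 = 33%) |

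This part needs no assumption beyond reading section 8.1.2 literally.

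**The case against.** **The text does not say that dislocation counts only after CT.** A reader might infer that a good OMAS rules a case out and that the endpoint is biased toward the Walker by construction. The protocol does not go that far. Section 10.2 says when a CT is made, not that a radiographic dislocation without CT is scored as absent. Section 8.1.2 has no score condition, and the two conditions might have been meant as alternatives. This objection stands: what can be said is that the case definition is unclear and, as written, may depend on OMAS.

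**The risk ratios are not estimates.** They apply a back-solved difference between whole arms to patients with a dislocation, who may score low whatever device they wear. A range that stopped at 0.58 would leave out plausible values near 1. This also stands, and the figures serve only to show what the rule could do.

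**Other safety data exist.** Section 8.1.3 names other complications such as deep vein thrombosis or surgery, assessed at t2 and t3, and section 9.2.1 records all adverse events reported or observed. Calling dislocation the only safety endpoint would be wrong. A displacement that becomes clinically apparent after t2 could still be recorded; the gap is in scheduled films.

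**The window may be loose wording.** The secondary objective speaks of a 6-week effect, and the parenthesis in 8.1.2 may mean only that events after placement count. The film is taken at the same time in both arms. The uncovered days are when controls first bear weight, so control events missed then would work against the Walker, opposite to the first problem. That makes this a wording conflict rather than further evidence of bias toward the Walker, but the two time origins still disagree.

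**The plan's existing 3 mm figure is not a ready substitute.** Section 1 states "The fracture is stable if there is a dislocation of less than 3 millimetres at the ‘medial clear space"’ on the Mortise view. That defines joint stability and not fracture displacement. It may not suit the isolated malleolus tertius fractures admitted in section 4.2, or SE4A fractures at t2, where no weight-bearing view is listed.

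**Conclusion.** The concern holds in a limited form. On the plain reading, confirmation of the dislocation endpoint depends on a low score on the unblinded primary outcome, and under Hypothesis 1 that can reduce confirmed cases more in the Walker arm. The protocol leaves open how a displaced film with a good score is counted, and the rule does not control the type I error of the between-arm test.

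The size of any bias is unknown. The range of apparent risk ratios, about 0.26 to 0.90, rests on a true ratio of 1, normal scores, a back-solved shift of 0.83 to 0.85 SD or half of it, and unconfirmed cases not being counted. With equal scores among dislocated patients the ratio is 1, although cases could still be missed and the endpoint would still depend on the primary outcome.

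The window mismatch is plain: 7 to 10 days, up to 14 at the entry limit, lie after the last scheduled film.

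Severity is moderate. The endpoint is secondary, section 11.4 expects dislocation rarely if ever, and 50 patients are planned in total. Imprecision may well outweigh a distorted ratio, though with so few events one case classified differently could change the safety conclusion.

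**What to change.** - In section 10.2, define the trial endpoint from the t1 and t2 radiographs regardless of OMAS. State one radiographic displacement criterion for all eligible fracture types, chosen by the investigators; it need not be the medial clear space figure in section 1.
- Report CT findings separately, and leave the clinical use of CT to the clinicians.
- Restate section 8.1.2 as dislocation between the t1 and t2 radiographs, with t2 at 6 weeks posttraumatic, so that it agrees with section 2, section 3 with Table 1, and section 10.2.
- Delete the sentence on type I error.

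The cost is protocol wording and agreement on a criterion, since the films are already planned in everyone at both visits. The downside is that some radiographic cases will lack CT confirmation, and films read by unblinded staff may include false positives.
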